## 13. STATISTICAL CONSIDERATIONS

### 13.1 Analysis of Outcome Measures

Analysis will follow intention to treat principles (ITT) Following data cleaning, levels of demographics gathered at primary screening will be quantified using basic statistics (mean, SD, Median, IQR) and graphical presentations (boxplots, histograms, scatter plots) Sub division will be made by intervention /control and stratum. Likewise levels of primary and secondary outcomes at baseline will be similarly reported. Prior to any substantial analysis, preliminary impression of trends in longitudinal measurements will be provided graphically, separately for intervention and control participants.

1. Linear mixed model analysis will be used to compare peak  $VO_2$  at two years between the intervention and the control group Covariates will be baseline peak  $VO_2$ , age, gender systolic/diastolic blood pressure and BMI measured at baseline. GP practices or recruitment centres will be included as random effects to enable findings from this trial to be judged in the context of a different group of GP practices

2. Further exploratory analyses will incorporate interaction terms between intervention/control and each of the covariates. Backward elimination will be used to remove non significant interactions and then non significant main effects. If residuals from mixed model analysis violate the assumption of a normal distribution as tested by Kolmogorov Smirnov test then transformation of the dependent variable or bootstrap analysis will be conducted. Transformations considered will be those in the Box Cox family i.e. power and log. Bootstrap analysis will involve sampling with replacement 1000 sets of data from the original data, each of the same size as the original dataset Each set will then be analysed in the same manner as the original dataset This will enable an empirical distribution of each test statistic to be formed and relocated at its null hypothesis value Significance of the statistics in the original data will then be determined from the appropriate tail area of the empirical null distribution.

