### 13.1.1 Power Calculations

We will send invitations to 1280 potential participants from 64 GP practices with the aim of recruiting 640 for further testing. 250 of the screened participants will then be randomised. In addition, suitable participants from outpatient clinics run by [name] and [name] will also be invited to take part.

Our primary outcome will be based on a 'gold' standard test of exercise tolerance defined by peak  $\text{VO}_2$  using CPET and assessed at baseline and after the treatment with the trial drug. We hypothesise that the spironolactone will improve peak  $\text{VO}_2$  compared to the placebo treated subjects. We base our power calculation for peak  $\text{VO}_2$  on the published values of peak  $\text{VO}_2$  in subjects with HFpEF ( $16 \pm 5$  ml/min/kg). We anticipate a difference of 2ml/min/kg in the improvement in peak  $\text{VO}_2$  after 2-year treatment with spironolactone compared with the control group. Unfortunately this publication does not give a standard deviation on the change in peak  $\text{VO}_2$  from baseline but a similar trial, Edelmann et al provides that statistic (5 ml/min/kg) and also reports a similar magnitude of effect.

A sample size of 100 patients in each group will have 80% power to detect a difference in means of 2.000 assuming that the common standard deviation is 5.000 (effect size =0.40) using a two group t-test with a 0.05 two-sided significance level. Sample size calculation was conducted using the nQuery software. Approximately, for 80% power at 5% significance, sample size in each group would be  $15.68/(\text{effect size})^2$ . To accommodate a loss to follow-up of 20% of patients from each group would imply initially recruiting a total sample size of 250 ( $250 \times 0.8 = 200$ ) in order to still retain 200 patients in all. Loss of 20% of patients would still enable effects in excess of 2.3ml/min/kg (effect size=0.46) to be detected with 90% power at the 5% significance level. Sample size= $21.0/(\text{effect size})^2$  for 90% power, 5% significance. At the other extreme zero loss to follow up from 250 patients would lead to 88% power to detect a 2 ml/min/kg at 5% significance Prediction of 20% loss to follow up is based on a 10% loss per year and composed of 5% due to death and 5% due to other reasons. The relevant population of patients would be under regular follow up and as such would have relatively lower expected mortality.

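### The fallback bootstrap is fixed at 1000 resamples, so a bootstrap p-value close to 0.05 carries avoidable resampling noise; the overall effect is small and the number is cheap to raise

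*Protocol*

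**What the plan says.** Protocol section 13.1 (Analysis of Outcome Measures), item 2, sets a fallback for mixed-model residuals that "violate the assumption of a normal distribution as tested by Kolmogorov Smirnov test then transformation of the dependent variable or bootstrap analysis will be conducted". The protocol gives no rule for choosing between the two remedies.

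For the bootstrap it fixes three things:

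- The number of resamples: "Bootstrap analysis will involve sampling with replacement 1000 sets of data from the original data".
- Re-centring: "This will enable an empirical distribution of each test statistic to be formed and relocated at its null hypothesis value".
- The decision: "Significance of the statistics in the original data will then be determined from the appropriate tail area of the empirical null distribution".

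Each resampled dataset is analysed in the same way as the original one, so each resample refits the mixed model. The secondary-outcome text that follows carries the modelling over to the secondary endpoints and adds separate runs in each stratum.

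The only significance level in the protocol is 5%. It appears in section 13.1.1 as a planning assumption: "using a two group t-test with a 0.05 two-sided significance level".

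**The concern.** On this route the p-value is a simulated proportion. With 1000 resamples, a decision at 0.05 turns on whether about 50 of the resampled statistics fall in the tail, and that count varies from run to run on identical data. A borderline result could therefore be called significant in one run and not in the next, for a reason unrelated to the patients. The protocol itself fixes the number that controls this noise, so the point does not depend on detail that an analysis plan would normally supply.

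**Working it through.** **Inputs.** From section 13.1, item 2: B = 1000 resamples, with significance from the tail area. From section 13.1.1: two-sided 5%, 100 evaluable patients per arm, difference 2 ml/min/kg, SD 5 ml/min/kg.

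**The protocol's own figures first.** The stated shortcut gives 15.68/0.40² = 98 per arm, against the stated 100. Power from the noncentral t distribution is 80.4% at 100 per arm (stated 80%), 88.3% at 125 per arm (stated 88%), and 89.9% for 2.3 ml/min/kg at 100 per arm (stated 90%). These reproduce. The protocol gives no Monte Carlo error for the bootstrap, so there is no stated figure to reproduce there.

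**Standard error of the bootstrap p-value.** Let p be the value that unlimited resamples would give. The number of resampled statistics in the tail is Binomial(B, p), so SE = √(p(1−p)/B).

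- B = 1000, p = 0.05: √(0.05 × 0.95/1000) = 0.0069. The 95% range over reruns is 0.05 ± 1.96 × 0.0069, about 0.036 to 0.064.
- B = 10,000: √(0.05 × 0.95/10,000) = 0.0022. The range is about 0.046 to 0.054.

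**Chance that one run falls on the wrong side of 0.05.** A result counts as significant if the simulated proportion is below 0.05, i.e. at most 49 of 1000 or 499 of 10,000. For example, at p = 0.045 and B = 1000 the chance is P(X ≥ 50) = 0.242; at p = 0.055 it is P(X ≤ 49) = 0.225.

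| Exact bootstrap p | B = 1000 | B = 10,000 |
|---|---|---|
| 0.030 | 0.04% | 0% |
| 0.040 | 6.6% | <0.1% |
| 0.045 | 24% | 0.9% |
| 0.048 | 40% | 18% |
| 0.052 | 37% | 18% |
| 0.055 | 23% | 1.3% |
| 0.060 | 7.8% | <0.1% |

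**Check on fixed data.** One simulated skewed dataset (100 per arm, SD 5) with a t-test p of 0.045 was bootstrapped with B = 1000 under 400 seeds. The bootstrap p ran from 0.028 to 0.062, and 16% of seeds gave a non-significant result. The mean bootstrap p was 0.043, a little further from 0.05 than 0.045, so 16% is in line with the table.

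**Overall size.** The table applies only once p is already close to 0.05. To see how often that matters, average the wrong-side probability over the sampling distribution of the result, assuming the bootstrap is always used. Take z as normal with mean δ/SE and unit SD, SE = 5 × √(2/100) = 0.707 ml/min/kg, and p = 2(1 − Φ(|z|)).

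| True difference δ (ml/min/kg) | Verdict differs from unlimited resamples, B = 1000 | B = 10,000 |
|---|---|---|
| 0 | 0.5% | 0.2% |
| 1.4 (near the worst case) | 1.9% | 0.6% |
| 2 (planned) | 1.3% | 0.4% |

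The changes go in both directions and nearly cancel. With B = 1000, type I error is 5.0% and power at 2 ml/min/kg is 80.6%, against 80.7% with unlimited resamples.

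**Sensitivity.** If the tail area means one tail doubled, the SE at B = 1000 is 2 × √(0.025 × 0.975/1000) = 0.0099. The wrong-side chance at p = 0.045 becomes 32%, and the overall rates become 0.8%, 2.7% and 1.9% for differences of 0, 1.4 and 2.

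**The case against.** The best case against is that this is a preference about computing. No part of the protocol contradicts the 1000, and no stated precision target is missed. Neither error rate is materially harmed, and two conditions must be met first: residual normality is rejected, and the bootstrap is preferred to a transformation. All of that stands, and it is why the point is minor.

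Three stronger readings are tempting, and the protocol does not support them.

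- **The trial has a one-in-four chance of a seed-driven verdict.** The 24% is conditional on an exact p of 0.045. The overall figure is 0.5% to 1.9%, or up to 2.7% with a doubled tail, even if the bootstrap is always used.
- **The primary conclusion is exposed.** The primary comparison is item 1 of section 13.1. The bootstrap is in item 2, which opens with exploratory analyses. Its trigger refers to mixed-model residuals, and the mixed model is also the primary method, so coverage of the primary comparison is possible but not stated.
- **The missing seed and Monte Carlo error reporting are defects.** An analysis plan may set both, and it is not at hand. A preset seed also makes a run repeatable without making it more accurate.

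The 1000 may also not be the effective total. Item 3 of section 13.1 plans 10 imputations and does not say how they combine with the bootstrap. If 1000 resamples were drawn within each imputed dataset, there would be 10 × 1000 = 10,000 per analysis, and the B = 1000 calculation might not apply. Imputation adds random variation of its own.

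What survives is that the protocol fixes a number, the number is low for a decision at a threshold, and raising it is easy.

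**Conclusion.** The point holds as a minor, optional improvement. With 1000 resamples, a bootstrap p-value near 0.05 has a standard error of about 0.7 percentage points, and verdicts between roughly 0.035 and 0.065 are noticeably unstable from run to run. Outside that zone 1000 is enough.

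The overall chance that the noise changes a verdict is about 0.5% with no effect, 1.3% at the planned 2 ml/min/kg and 1.9% near 1.4 ml/min/kg. These figures assume 100 evaluable patients per arm, SD 5, a normal approximation, a two-tail count, one set of 1000 resamples per analysis, and a bootstrap that is always used. The last assumption makes them upper figures for this route, since both gating conditions reduce the chance further. Sample size, type I error and power are not called into question.

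**What to change.** In section 13.1, item 2, replace 1000 sets by at least 10,000 sets. The standard error at p = 0.05 falls from 0.69 to 0.22 percentage points, the wrong-side chance at an exact p of 0.045 falls from 24% to 0.9%, and the overall rates fall to about 0.2%, 0.4% and 0.6% (differences of 0, 2 and 1.4 ml/min/kg).

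This reduces seed dependence without removing it: an exact p of 0.048 is still misread in 18% of runs.

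The cost is computing time, about ten times as many model fits. Each resample refits a mixed model with practice or centre as a random effect, possibly across imputations, endpoints and strata, so the extra load is more than trivial but feasible for a trial of 250 patients. No data collection, staff time or patients are affected.

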Secondary analyses will also use linear or non linear mixed modelling as above but with dependent variable the secondary end points mentioned in the earlier Trial End Points section Interactions between intervention/control, and age and gender will also be included in the mixed modelling analyses to see whether differences in secondary endpoints between intervention and control participants vary with these two factors. Each mixed model analysis will be run additionally separately on each stratum. The primary QoL analysis will be the change in the overall QoL score between treatment groups over the two year duration. This will include baseline measures as a covariate. Full analysis will therefore be completed at the 24 months period and this will form the principle QoL analysis. The 12 month QoL assessments will allow a preliminary analysis to be undertaken to determine if changes occur within the first 12 months. These repeated measures will allow further exploratory analysis of changes in QoL to be undertaken to explore which domains are driving the changes in the QoL scores.

3. Missing values will be substituted using a multiple imputation procedure. Because of the likelihood of non normality the method of Hussain will be used. This replaces the data by its Normal scores, imputes using these transformed data and then uses a polynomial relationship between Normal scores and untransformed data to give a complete set of data. This is then repeated 10 times and variation seen between repetitions and within are used to estimate the uncertainty in the imputed mean value.

In the case of missing data due to death of the participant during the trial a comparative analysis will be conducted between surviving participants and the deceased. If no difference is apparent then MI will be performed on all of the data but otherwise a complete case analysis will be conducted and a report compiled setting out the difference between the deceased and the surviving participants.

|                          |            |               |            |       |          |
|--------------------------|------------|---------------|------------|-------|----------|
| Trial name:              | IMPRESS-AF |               |            |       |          |
| Protocol version number: | 6.0        | version date: | 12/10/2015 | Page: | 45 of 67 |

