Considering the power available for secondary endpoints, Conraads et al (the ELANDD trial) give sufficient statistical information to investigate this issue for 6 minute walk distance. Comparing the difference in change from baseline between a control group (n=59) and an intervention group (n=57) using nebivolol (26m difference), gave a t statistic p value of .004. This combination of t statistic and difference between groups implies an SD on change from baseline of 48m and a power of 96% to detect a 26m difference with a sample size of 100 in each group. With our larger sample size (n=100) in each group, a smaller difference of around 18m between the two groups could be detected with 80% power for 5% significance.

Returning to Edelmann et al they supply a 95% confidence interval on the difference between two groups in change from baseline for E/e'. This confidence interval (-4.3 to -2.1) together with the mean difference (-3.2) allows estimation of the SD for change from baseline in E/e'. (SD=2.08) In turn that enables a power calculation to be performed which reveals in excess of 99% power to detect a -3.2 difference in change from baseline between intervention and control group with our sample size of 100 in each group.

From the same paper and following the same steps (95% confidence interval -11 to 1 and mean difference -5) leads to an SD of 11.35 for change from baseline) In turn that suggests 87% power for MLWHFQ showing at 5% significance a difference in change from baseline of 5 units.

As well as influencing power, sample size influences precision of estimation. The 95% confidence intervals in the table indicate the precision of the mean endpoint (difference between intervention and control in change from baseline to two years). None of the confidence intervals contain zero indicating a significant effect of the intervention

|                          |            |               |            |       |          |
|--------------------------|------------|---------------|------------|-------|----------|
| Trial name:              | IMPRESS-AF |               |            |       |          |
| Protocol version number: | 6.0        | version date: | 12/10/2015 | Page: | 46 of 67 |

| Endpoint             | Mean endpoint | SD endpoint | SE endpoint | Lower 95%CI | Upper 95%CI |
|----------------------|---------------|-------------|-------------|-------------|-------------|

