#### *Sample size – calculations and conclusions*

We estimate that a sample size of 100 participants in each arm would give power of at least 80% to detect differences in primary and secondary endpoints of a magnitude consistent with published results from similar studies. Inclusion of provision for a 20% drop out rate could potentially lead to powers of near 90% or more if the assumption of a drop rate of 20% was too pessimistic.

|                          |            |               |            |       |          |
|--------------------------|------------|---------------|------------|-------|----------|
| Trial name:              | IMPRESS-AF |               |            |       |          |
| Protocol version number: | 6.0        | version date: | 12/10/2015 | Page: | 47 of 67 |

---

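### Read literally, the secondary models adjust 6MWT and E/E' for baseline peak VO2 but not for their own baselines, and include treatment interactions without naming the model or contrast that gives the overall effect

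*Protocol*

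**What the plan says.** Section 13.1, item 1, compares peak VO2 at two years in a linear mixed model. The covariates are baseline peak VO2 and "age, gender systolic/diastolic blood pressure and BMI measured at baseline", with practice or recruitment centre as a random effect. Item 2 confines treatment-by-covariate interactions to further exploratory analyses, with backward elimination.

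For the other endpoints the section says: "Secondary analyses will also use linear or non linear mixed modelling as above but with dependent variable the secondary end points". It then says: "Interactions between intervention/control, and age and gender will also be included in the mixed modelling analyses". The same sentence gives the purpose, which is to see whether treatment differences vary with age and gender. For quality of life only, the section states that baseline measures will be a covariate.

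Section 2.2 has both 6MWT and E/E' assessed at baseline and at two years. Section 13.1.1 bases their power on the SD of change from baseline; for 6MWT the cited trial "implies an SD on change from baseline of 48m and a power of 96% to detect a 26m difference".

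**The concern.** Two things are left loose.

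**Baseline covariate.** If only the dependent variable changes, the one functional baseline in the 6MWT and E/E' models is peak VO2. The covariate that usually explains most of the variance in a repeated measure, its own baseline, is absent. The analysis then does not match the power calculation.

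**Overall effect.** With treatment-by-age and treatment-by-gender terms in the model, the meaning of the treatment coefficient depends on coding. With age in years and gender coded 0/1, it is the effect at age 0 in the reference gender, although the lowest eligible age is 50 (section 4.1.1). The primary endpoint has a main-effects model in item 1 and interactions apart in item 2. The secondary endpoints have no such separation.

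Two analysts following the text could report quite different p-values for the same secondary endpoint.

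**Working it through.** **Inputs from section 13.1.1.** 100 per group after 20% loss; two-sided 5%. Difference and SD of change: 6MWT 26 m and 48 m; E/e' 3.2 and 2.08; MLWHF 5 and 11.35.

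**Assumptions (not in the protocol, so shown as ranges).** ρ is the correlation between baseline and two-year values, 0.5 to 0.9, with equal SDs at both times. r is the correlation between baseline peak VO2 and the outcome, 0 to 0.5. Mean age is 65 to 75 with SD 7 to 10. The share p in the non-reference gender is 20% to 50%.

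**Step 1: reproduce the stated power.** Power = Φ(δ/SE − 1.96), with SE = SD × √(2/100).
- 6MWT: SE = 48 × 0.1414 = 6.79 m; 26/6.79 = 3.83; power 96.9% (stated 96%).
- E/e': SE = 0.294; power above 99.9% (stated above 99%).
- MLWHF: SE = 1.61; power 87.6% (stated 87%).

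All three reproduce.

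**Step 2: which baseline is in the model.** From SD of change = SD × √(2(1 − ρ)):
- two-year value adjusted for peak VO2 only: SD = 48/√(2(1 − ρ)) × √(1 − r²)
- own-baseline ANCOVA: SD = 48 × √((1 + ρ)/2)

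| ρ | 6MWT SD, two-year value, r = 0 / 0.5 | Power for 26 m | ANCOVA SD | Power |
|---|---|---|---|---|
| 0.5 | 48.0 / 41.6 | 96.9% / 99.3% | 41.6 | 99.3% |
| 0.7 | 62.0 / 53.7 | 84.3% / 92.9% | 44.3 | 98.6% |
| 0.8 | 75.9 / 65.7 | 67.8% / 79.9% | 45.5 | 98.1% |
| 0.9 | 107.3 / 93.0 | 40.3% / 50.7% | 46.8 | 97.6% |

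If change from baseline is the dependent variable, the SD is at most 48 m and the stated power is kept. ANCOVA still improves on it (41.6 to 46.8 m). The same formulas for E/e' with two-year values give at least 99.8% power across the range.

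**Step 3: interaction terms.** Relative to Step 1, the variance of the treatment coefficient is multiplied by:
- age uncentred, gender 0/1: 1 + (mean age/SD age)² + p/(1 − p)
- age centred, gender 0/1: 1 + p/(1 − p)
- both centred: 1

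Example: mean 72, SD 8, p = 0.3 gives 1 + 81 + 0.43 = 82.4. The SE is √82.4 = 9.08 times larger, so for 6MWT 6.79 × 9.08 = 61.6 m.

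| Coding | 6MWT | E/e' | MLWHF |
|---|---|---|---|
| Uncentred (SE 6.6 to 10.8 times larger) | 6-9% | 17-38% | 6-8% |
| Age centred, gender 0/1 | 77-93% | >99% | 60-80% |
| Both centred | 96.9% | >99.9% | 87.6% |

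Simulation of 4,000 trials at mean age 72, SD 8, p = 0.3 agrees: 6MWT 6.2% uncentred and 96.6% centred; MLWHF 6.7% and 87.7%.

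**The case against.** A reader might infer that the treatment coefficient in every secondary model is the effect at age zero, and that 6MWT power therefore falls from 97% to about 7%. The protocol does not support that. The figure needs uncentred age, 0/1 gender, no elimination and an analyst who reports that coefficient as the overall effect, and the protocol prescribes none of these. The sentence on interactions states an effect-modification purpose and can be read as describing an added analysis. The words carrying the primary approach over may also bring in item 2's backward elimination. Simulated with elimination at 5% and no true interaction (100 per arm, age 72 ± 8, 60% men, uncentred), an interaction stayed in about 9% of trials and power for the treatment term was about 93%. Centring, or a marginal contrast, is the kind of detail that an SAP may settle.

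A reader might also infer that all secondary endpoints lack own-baseline adjustment. They do not. Quality of life has it. Hospitalisation is a rate over follow-up, and sinus rhythm has no varying baseline because all participants enter in permanent AF. For 6MWT and E/E', section 2.2 speaks of improvement and section 13.1.1 of change from baseline, so change may be the intended dependent variable, and then no stated power is lost.

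All of this stands, and it limits the size of the point. It does not supply what is missing: the text names neither the model for the overall effect nor the own baseline for 6MWT and E/E', although it does both for the primary endpoint. Elimination is not a full answer either, since the meaning of the treatment coefficient would then depend on interaction p-values.

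**Conclusion.** The point holds in limited form, as a free improvement and not as a demonstrated error in the effect estimate or a demonstrated loss of power.

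- **Own baseline (6MWT and E/E' only).** For 6MWT there is a material loss only if two-year values are modelled and ρ is above about 0.5; it is large at 0.8 to 0.9. E/E' stays above 99% on this point under the protocol's own effect and SD.
- **Interactions.** Power for the treatment coefficient is lost with uncentred covariates and reduced with partial centring. In the partly centred case MLWHF falls to 60-80%, at or below the section 13.1.1 conclusion that "a sample size of 100 participants in each arm would give power of at least 80" per cent. Nothing is lost if both covariates are centred or a marginal contrast is reported.

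ρ, r, the age distribution and the gender split are assumptions, so the ranges matter more than any single figure.

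**What to change.** In section 13.1, or in the SAP:

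1. State that the overall treatment effect on each secondary endpoint comes from a main-effects model without treatment interactions. For 6MWT and E/E', add the endpoint's own baseline to the listed covariates. Quality of life already has this; hospitalisation rate and sinus rhythm need none.
2. State that treatment-by-age and treatment-by-gender terms are fitted in separate exploratory models, as item 2 does for the primary endpoint.

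The cost is two sentences. Both baselines are already collected, and the sample size and visit schedule do not change. Own-baseline ANCOVA is more precise than change scores at any ρ below 1. Because the own baseline is added to the listed covariates and replaces none of them, it costs at most one degree of freedom against a model of two-year values.

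### Ten imputations are few for a primary outcome with 20% planned loss: valid, but a near-threshold result can change with the random seed

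*Protocol*

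**What the plan says.** Protocol section 13.1, item 3, opens with "Missing values will be substituted using a multiple imputation procedure". The method transforms the data to Normal scores, imputes, and transforms back. The number of repetitions is then fixed: "This is then repeated 10 times and variation seen between repetitions and within are used to estimate the uncertainty in the imputed mean value".

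The same item has a second branch for outcomes missing because of death. Survivors and deceased participants are compared. If no difference appears, all missing data are imputed; "otherwise a complete case analysis will be conducted and a report compiled".

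Section 13.1.1 sets the expected loss: "To accommodate a loss to follow-up of 20% of patients from each group would imply initially recruiting a total sample size of 250". It also explains the figure: "Prediction of 20% loss to follow up is based on a 10% loss per year and composed of 5% due to death", with the other 5% per year due to other reasons. The assessment table in section 8 lists cardiopulmonary exercise testing at baseline and month 24 only.

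**The concern.** Multiple imputation draws random values, so the pooled estimate carries simulation noise that shrinks as the number of imputations m grows. How much noise matters depends on the fraction of missing information (FMI). Here there is no intermediate exercise test from which to predict a missing month-24 value, so the FMI may be close to the missing proportion itself.

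If m is too small, two analysts who follow the plan on the same data with different seeds can report different p-values and, close to 0.05, opposite conclusions on the primary endpoint. That noise buys nothing, and more imputations would remove most of it.

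**Working it through.** **Inputs from the protocol.** m = 10 (13.1, item 3); 250 randomised, 20% lost, 100 completers per arm; difference 2 ml/min/kg; SD 5; two-sided 0.05 (13.1.1).

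**Assumed.** FMI about 0.2, range 0.1 to 0.3. The protocol does not give it. The centre of the range is the planned missing proportion. Informative auxiliary variables would lower it.

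**1. The plan's own figures.** The basis is "A sample size of 100 patients in each group will have 80% power to detect a difference in means of 2.000"; the SD is taken as 5.
- SE of the difference = 5 × √(2/100) = 0.71; 2/0.71 = 2.83.
- Power by the noncentral t distribution: 80.4% with 100 per arm, and 88.3% with 125 per arm.
- 200/0.8 = 250.

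The stated 80%, 88% and 250 all reproduce.

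**2. Size of the simulation noise.**
- Relative efficiency = 1/(1 + FMI/m) = 1/(1 + 0.2/10) = 0.980.
- Monte Carlo SE of the pooled effect = √(FMI/m) × SE.
- m = 10: √(0.2/10) × 0.71 = 0.141 × 0.71 = 0.10 ml/min/kg.
- m = 100: √(0.2/100) × 0.71 = 0.045 × 0.71 = 0.03 ml/min/kg.

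**3. What the noise does to the p-value.** Hold one dataset fixed and vary only the seed. The total variance at infinite m is scaled to 1, with a share FMI between imputations and 1 − FMI within. The between variance is drawn as FMI × χ²(m − 1)/(m − 1), the estimate is shifted by a normal error with variance FMI/m, and the results are pooled by Rubin's rules with Barnard-Rubin degrees of freedom. At FMI 0.2:

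| p at infinite m | 95% range, m = 10 | seeds crossing 0.05, m = 10 | 95% range, m = 100 |
|---|---|---|---|
| 0.005 | 0.002 to 0.018 | 0% | 0.004 to 0.007 |
| 0.02 | 0.008 to 0.053 | 3.5% | 0.015 to 0.027 |
| 0.03 | 0.013 to 0.073 | 15% | 0.023 to 0.039 |
| 0.05 | 0.023 to 0.108 | at the threshold | 0.039 to 0.064 |
| 0.08 | 0.040 to 0.158 | 8% | 0.065 to 0.099 |

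The first row is about the result expected at the design effect, since a standardised effect of 2.83 corresponds to p of about 0.005. A patient-level check (250 patients, 20% missing, 1000 seeds) at p = 0.05 gave 0.022 to 0.114 with m = 10 and 0.039 to 0.065 with m = 100.

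**4. How often it would matter.** Simulate trials at the design effect and analyse each with two seeds.

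| FMI | disagree, m = 10 | disagree, m = 100 | power, m = 10 | power, m = 100 |
|---|---|---|---|---|
| 0.1 | 3.6% | 1.1% | 80.0% | 80.4% |
| 0.2 | 5.8% | 1.6% | 79.0% | 80.3% |
| 0.3 | 7.9% | 2.2% | 78.1% | 80.1% |

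Repeat simulations moved these rates and powers by no more than about 0.2 percentage points. Under the null at FMI 0.2, two seeds disagree in 2.2% of trials with m = 10 and 0.7% with m = 100. Type I error is about 4.8% to 4.9% at either m.

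**5. Sensitivity to the residual SD.** The planned model adjusts for baseline. If baseline and month-24 values correlate at 0.5 (an assumption), the residual SD is 5 × √(1 − 0.25) = 4.33. Disagreement at a true effect of 2 is then 4.3% with m = 10 and 0.9% with m = 100; power is 88.8% against 90.0%. The pattern is the same and the rates are somewhat lower.

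**The case against.** The strongest defence is that nothing here is wrong as inference. Rubin's variance already includes the finite-m noise, type I error holds, and efficiency is 98% of the maximum. Some seed dependence remains at any finite m, and no standard in the protocol makes 10 wrong and 100 right. All of this stands. It limits the point to reproducibility and rules out any claim of bias or inflated error.

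Three stronger readings are tempting, and the protocol does not support them:

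- **That the primary p-value in general hangs on the seed.** It does so materially only for p between roughly 0.02 and 0.08. At about the result expected under the design effect, no seed crossed 0.05.
- **That imputation merely returns the complete-case adjusted estimate plus noise.** That assumes imputation from the analysis covariates alone, and item 3 does not list the imputation variables. Baseline walk distance, 12-month quality of life, and repeated blood pressure and renal measurements are collected and could reduce the FMI; hence the range down to 0.1.
- **That the variance is attached to the wrong quantity.** Item 3 speaks of an imputed mean, whereas section 13.1 tests a treatment difference. Combining variation between and within repetitions is a common short description of Rubin's rules, and nothing says that the treatment coefficient will not be pooled. The wording is loose, but a wrong analysis is not shown.

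It is also fair that m has no role if survivors and deceased participants differ and complete cases are analysed. About half of the predicted loss is death, so that branch is realistic. The rates above apply only when imputation is used. The seed and the reporting of Monte Carlo error are commonly left to the analysis plan, and their absence here is no fault.

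**Conclusion.** The point holds as a minor one. The protocol itself fixes m at 10, so this is a stated choice and not missing detail. At an assumed FMI of 0.2 (range 0.1 to 0.3), the significance of the primary result would differ between two seeds in about 6% (3.6% to 7.9%) of trials at the design effect, against about 1.6% (1.1% to 2.2%) with 100 imputations. The power cost is about one point, 79% against 80%, in a design set at 80% with no reserve once the planned loss has occurred.

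The validity of the primary analysis is not threatened. The figures rest on the assumed FMI, on SD 5 from the sample-size section, and on standard normal-theory imputation. The Normal-scores back-transformation and the practice or centre random effects were not simulated.

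**What to change.** In section 13.1, item 3, change the number of repetitions from 10 to about 100, and add one clause stating that the between- and within-imputation variances are combined by Rubin's rules for the treatment coefficient of the mixed model.

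The cost is one number, one clause and some computing time. Section 13.1 already allows for 1000 bootstrap datasets, so computing is unlikely to be a constraint. Sample size, data collection and the complete-case branch are unaffected.
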